**Methods:**

A pragmatic randomized controlled trial (RCT) is planned with two study groups (SHAFT-Young and SHAFT-Elderly). A total of 287 eligible acute humeral shaft fractures are scheduled to be recruited and randomly allocated to surgical or non-surgical treatment with the option of early crossover due to delayed union. The surgical method within the allocation is decided by the surgeon. The primary outcome is the Disability of Arm, Shoulder, and Hand (DASH) score at 52 weeks, and is assessor blinded. The secondary outcomes are DASH score, EQ-5D-5L, pain assessed by visual analog score, Constant-Murley score including elbow range of motion, and anchor questions collected at all timepoints throughout the trial. All complications will be reported including; infection, nerve or vascular injury, surgical revisions (implant malpositioning, hardware failure, aseptic loosening, and peri-implant fracture), major adverse cardiovascular events, and mortality.

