### Trial design

A pragmatic multicenter, randomized, controlled, outcome assessor-blinded, clinical superiority trials. The steering committee which consist of trauma- and shoulder-elbow surgeons have assessed the pragmatic design using PRECIS-2 [33] which yielded 37 points out of the possible 45 points (Fig. 1). An explanation for each domain score is provided in Appendix 1. This study furthermore collaborates with the NORCRIN Work Package 13 network.

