### Randomization

A computerized database software, Research Electronic Data Capture (REDCap)© [38] will be used to generate an irreversible random allocation sequence and perform block randomization with selected block sizes of 2 and 4, which will be stratified on site and age (18–64 and +65). Patients will be assigned to the trial with an allocation of 1:1 to either surgical treatment or non-surgical treatment. The trial worker acquires the allocated treatment from the central coordinator with randomization rights to REDCap. The trial worker then initiates the treatment, either by scheduling the surgery date or applying the chosen non-surgical method.

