### Blinding

The trial will consist of several levels of blinding:The primary outcome will be blinded to everyone involved in the trial, apart from the patients and a central trial worker (non-physician), who will only review the questionnaire for completion in REDCapThe statistical analysis will be conducted by a blinded biostatistician

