### Primary outcome measure

The primary outcome is the DASH score at 52 weeks [3]. The DASH will also be assessed at pre-injury, 6, 12 and 26 weeks, and 2 and 5 years. The DASH score is a 30-item self-reporting patient-reported outcome measure specific for physical function and symptoms of the upper limb. Scores range from 0 (no disability) to 100 (most severe disability). The DASH score is validated for the target population [39] and has undergone cross-cultural adaptation in Danish, Swedish and Norwegian [40].

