*Q: Overall, how would you describe your general health now, compared to after the (operation / non-surgical treatment)?*
RO: Much worse, A little worse, About the same, A little better, Much better
*Q: Overall, how would you describe your upper arm now, compared to after the (operation/non-surgical treatment)?*
RO: Much worse, A little worse, About the same, A little better, Much better
*Q: How would you describe the change in physical function in your upper arm since after the (operation/non-surgical treatment)?*
RO: Much worse, A little worse, About the same, A little better, Much better
*Q: How would you describe the change in pain from your upper arm since after the (operation/non-surgical treatment)?*
RO: Much worse, A little worse, About the same, A little better, Much betterBinary repeat treatment question (BRT) presented with a binary response option:

*Q: With the knowledge and experience you have gained of the treatment; would you then choose the same treatment again for a similar fracture?*
RO: Yes, No

The DASH, EQ-5D-5L, and CA questions will be sent by email or mail and patients are asked to complete the questionnaires before visits. The questionnaires will be reviewed for missing data by a trial worker and patients will be assisted with completing the questionnaires if any data is missing, without interference from the medical staff. The trial worker collects the missing values before consultation with the physician. The physician then collects the additional outcome measures at the consultation and enters data directly into REDCap.

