The DASH questionnaire is adopted by the study group as the primary outcome as it is the best psychometrically validated and cross-culturally adapted PROM for humeral shaft fractures [39, 62]. The full DASH questionnaire is preferred over the QuickDASH by patients through simple semi-structured interviews. The interviews were simple in a sense that the objective was to determine the “most preferred” questionnaire rather than assess the content validity of each questionnaires [63]. The moderator was instructed in the conduct of qualitative interviews by an expert in qualitative research, but not properly trained. This could give challenges with bias, if the moderator preferred one questionnaire. This was sought to be reduced by the semi-structured guide, which was intended to make patients reflect, firstly on their treatment course and secondly on the questionnaires and its relevance, comprehensibility, and comprehensiveness, to induce a thought-through answer to the question: “Which questionnaire do you prefer?”

Through the interviews, it was furthermore recognized that around half of the patients failed to complete one or more questions, but none more than three, which is the cut-off for the score calculation to be valid [3]. To provide a margin of security for missing data, an unveiling trial worker will review the questionnaire for missing answers. Finally, to prevent performance bias, patients will complete the DASH questionnaire prior to visits with the physician, thereby blinding the physician.

The SHAFT trial is a pragmatic multicenter RCT, that will compare the effectiveness between surgical treatment versus non-surgical treatment in humeral shaft fractures, including a variety of fracture morphology, while taking the dilemmas within the population into account by splitting the population by age and providing the orthopedic society with an interval for early cross-over surgery.

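### The primary DASH is called assessor-blinded although unblinded patients rate it themselves, and the protocol article describes the trial worker's part in completing the form in two ways that do not agree

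*Protocol article*

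**What the plan says.** The Trial design section describes the study as "A pragmatic multicenter, randomized, controlled, outcome assessor-blinded, clinical superiority trials". The abstract attaches the property to the primary endpoint itself: "The primary outcome is the Disability of Arm, Shoulder, and Hand (DASH) score at 52 weeks, and is assessor blinded".

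Primary outcome measure defines the instrument: "The DASH score is a 30-item self-reporting patient-reported outcome measure specific for physical function and symptoms of the upper limb". The Blinding section says that the primary outcome is "blinded to everyone involved in the trial, apart from the patients and a central trial worker (non-physician"), and limits this worker's task to checking in REDCap that the form is complete. The same section says that the biostatistician is blinded. The Discussion adds that patients fill in the DASH before seeing the physician, and that this blinds the physician.

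The text after the anchor questions, under Secondary outcome measures, gives a wider procedure: "patients will be assisted with completing the questionnaires if any data is missing, without interference from the medical staff". It goes on to have the trial worker gather the missing answers before the consultation. On how often blanks occur, the Discussion reports from the preparatory interviews that "around half of the patients failed to complete one or more questions, but none more than three, which is the cut-off" for a valid score.

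**The concern.** Two statements about the primary outcome do not fit the rest of the article.

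First, assessor blinding is a property of whoever makes the rating. For a self-reported questionnaire that is the patient, and the patient is unblinded. Keeping the physician from the answers is useful, but the physician does not rate the DASH. A reader who relies on the abstract or the design line may credit the primary endpoint with a protection that it lacks.

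Second, checking a form for completeness and assisting a patient to complete it are different acts. The exemption granted under Blinding rests on the narrow task, and the procedure described later is the wider one. Nothing in the article limits what assistance may consist of. The phrase about medical staff keeps clinicians out but sets no condition on the worker. This leaves a possible route of influence on the primary outcome, which the plan could close at almost no cost.

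**Working it through.** **Label against the article's own definitions**

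| Question | Answer in the article | Section |
|---|---|---|
| What is claimed? | Trial and primary DASH are assessor-blinded | Trial design; abstract |
| Who rates the DASH? | The patient | Primary outcome measure |
| Is the patient blinded? | No, expressly exempt | Blinding |
| Who is described as blinded? | The physician, by completion before the visit; the biostatistician | Discussion; Blinding |

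The claimed property and the rater do not meet in any row.

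**Worker's role**

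| Section | Role |
|---|---|
| Blinding | Checks for completion, nothing more |
| Secondary outcome measures | Patients are assisted with missing items; the worker gathers the missing answers |
| Discussion | Reviews the form for missing answers |

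The first and second rows cannot both describe the limit of the role. On masking, the article neither says that this worker is masked to allocation nor that the worker knows it.

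**Is assistance needed to obtain a score?** By the Discussion, interviewed patients left at most three questions blank, and up to three still gives a valid score. Forms like those could be scored without help. The share of around half is reported with no numerator or denominator, so it cannot be recomputed.

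**Illustrative size**

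Inputs from the article: 30 items, range 0 to 100, at most three blanks, target differences of 7 (SHAFT-Y) and 10 (SHAFT-E). Assumptions: five options per item (four steps), equal weights, half of the patients in one arm affected, all shifts in the same direction, none in the other arm.

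- One item, one category: 100 / (30 × 4) = 0.83 points for that patient.
- Three items, one category each: 3 × 0.83 = 2.5 points.
- Arm mean, half affected: 0.5 × 0.83 = 0.42 points, or 0.5 × 2.5 = 1.25 points.
- Relative to 7 points: 0.42 / 7 = 6%; 1.25 / 7 = 18%.
- Relative to 10 points: 0.42 / 10 = 4%; 1.25 / 10 = 12.5%.
- Both arms shifted alike: difference between arms = 0.

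As a further illustration, take 85% of the planned numbers, so n per arm = 163 × 0.85 / 2 = 69.3 and 124 × 0.85 / 2 = 52.7. The standard error of the difference is SD × √(2/n): 14.91 × √(2/69.3) = 2.53 in SHAFT-Y and 18.59 × √(2/52.7) = 3.62 in SHAFT-E. Testing two-sided at 0.0471, a differential shift b with no true effect gives a rejection probability of 1 − Φ(1.985 − b/SE) + Φ(−1.985 − b/SE).

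| b | SHAFT-Y | SHAFT-E |
|---|---|---|
| 0.42 | 0.050 | 0.049 |
| 1.25 | 0.074 | 0.060 |

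**The case against.** The best defence is that nothing is hidden. The article calls DASH self-reported, names patients as unblinded and says that completion before the visit blinds the physician. Patients cannot be blinded to surgery versus a brace, so no design change is available. The article may also use assistance to mean no more than a prompt to fill in blanks, with the script left to the full protocol. Gathering a patient's own answer can reasonably be preferred to scoring around a blank, and the Discussion gives a safety margin against missing data as the reason. Three blanks at most among interviewees does not guarantee the same in 287 patients over repeated mailings.

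Much of this stands. The fault is one of label and role description, not concealment, and a benign reading of assistance is possible. What does not stand is the label itself: the abstract applies it to the DASH by name, and disclosure elsewhere does not make it correct. Nor does the benign reading settle the conflict between the two role descriptions, since the text does not confine assistance to a prompt.

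A reader might infer more, and the article does not support it:

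- *That the worker knows the allocation.* The exemption under Blinding can be read as permission to see outcome data, which checking a form requires. The Discussion's adjective for the worker (*unveiling*) is ambiguous. Under Randomization, "The trial worker then initiates the treatment, either by scheduling the surgery date or applying the chosen non-surgical method", but that worker obtains the allocation from a central coordinator and is not shown to be the central worker who reviews questionnaires.
- *That the worker helps choose the answers.* No section says so.
- *That strong treatment preferences are expected in this trial.* The Background reports strong physician preference in a different, completed study, and physicians are kept away from the DASH here.
- *That half of the trial's questionnaires will be affected.* The figure comes from pre-trial interviews of unstated size, in which patients completed both DASH and QuickDASH.

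**Conclusion.** The point holds as a mislabelled primary outcome and an internal conflict over the worker's role. The DASH is rated by unblinded patients. Only the physician (with respect to the DASH answers) and the biostatistician are described as blinded. The worker is limited to a completeness check in one section and takes part in obtaining missing answers in another, with masking to allocation left unstated.

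No bias is demonstrated. The range of about 0.4 to 1.25 points is a one-arm scenario. It rests on assumed item scaling, a shift in a single direction, and an interview-based frequency that may not carry over to the trial. The upper end also gives every affected patient the full three items. It would be wrong to quote 18% of the SHAFT-Y target, or a type I error of 0.074, as an expected distortion. With equal help in both arms the effect on the comparison is nil, and nothing in the article indicates a difference between arms. The case for a change is that the stated safeguard is inaccurate and the possible route of influence is easy to close.

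**What to change.** 1. In the abstract and the Trial design section, replace the assessor-blinded label for the primary outcome with a plain description: patient-reported, patients not blinded, physician kept from the DASH answers, statistician blinded. Interpret the primary result in that light.
2. Reconcile Blinding with Secondary outcome measures. The worker, or REDCap, flags blank items with a neutral prompt, and the patient alone answers or declines. Mailed forms go back with the blanks marked.
3. Score forms that still have up to three blanks by the rule that the Discussion already cites.
4. State whether the worker is masked to allocation.

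The change needs wording and a form setting, with no effect on sample size or visits. The price is a few more blank items, which the scoring rule tolerates up to its cut-off, and a less favourable blinding label.

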### Secondary outcome measures

Secondary outcomes consist of the DASH score, a self-reported measure of health-related quality of life (EQ-5D-5L), complication rates, visual analog scale (VAS) for pain from the arm, a functional outcome score (Constant-Murley), and anchor questions including clinical anchors, retrospective global transition questions and a binary repeat treatment question. Secondary outcome measures will be assessed at baseline, 6 weeks, 12 weeks, 26 weeks, and 52 weeks (Fig. 3):DASH score at earlier timepoints than 52 weeks (MIC [39], 7 and 10 respectively to age 18–64 and 65+)General health status questionnaire measured by EQ-5D-5L [41] (MIC [42], 0.074)Complications after treatment will be recorded and include local complications, early general complication, and mortality:Local complications: Infection (needing antibiotic treatment with or without debridement), nerve or vascular injury, surgical revision (due to implant malpositioning, hardware failure, aseptic loosening, or peri-implant fracture), and tolerance problems with a brace (discomfort resulting in non-compliance of wearing the braceEarly general complications needing hospitalization within 12 weeks from primary and secondary treatment [43, 44]:Major adverse cardiac events (MACE) including myocardial infarction, heart failure, cardiomyopathy and cardiac arrythmias.Other major adverse events include all-cause hospitalization other than the defined MACE.MortalityPain is assessed by using VAS. Patients are asked to assess their overall pain from the arm from 0 to 100 in a day (MIC [45], 16.55mm)Constant-Murley score [46] (MIC [39], 6.1). The subscales of strength and range of motion (ROM) will be depicted. ROM (flexion-extension) of the elbow will be recordedClinical anchor (CA) questions were presented with 5 response options (RO) and analyzed as a 5-point Likert scale:

Q: In general, would you say your health is?RO: Excellent, Very good, Good, Fair, Poor
*Q: How would you describe the results of the (operation/non-surgical treatment)?*
RO: Excellent, Very good, Good, Fair, Poor
*Q: How would you describe the function of your upper arm?*
RO: Excellent, Very good, Good, Fair, Poor
*Q: How would you describe the pain from your upper arm?*
RO: None, Mild, Moderate, Severe, ExtremeRetrospective global transition questions (RGTQ) presented with 5 response options and analyzed as a 5-point Likert scale:

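### Pain VAS, and on the literal text the global transition and repeat-treatment questions, are left to the visit physician although a protected pre-visit questionnaire already exists

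*Protocol article*

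**What the plan says.** The section on secondary outcome measures splits data collection in two.

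- Before the visit: "The DASH, EQ-5D-5L, and CA questions will be sent by email or mail and patients are asked to complete the questionnaires before visits". A trial worker checks these forms and helps with missing items, with medical staff kept out: "The trial worker collects the missing values before consultation with the physician".
- At the visit: "The physician then collects the additional outcome measures at the consultation and enters data directly into REDCap".

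The same section lists the secondary outcomes. They include Constant-Murley with elbow motion, complications, a pain VAS ("Patients are asked to assess their overall pain from the arm from 0 to 100 in a day") and "anchor questions including clinical anchors, retrospective global transition questions and a binary repeat treatment question".

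On blinding, the Trial design section describes "A pragmatic multicenter, randomized, controlled, outcome assessor-blinded, clinical superiority trials". The Blinding section is narrower: "The primary outcome will be blinded to everyone involved in the trial, apart from the patients and a central trial worker (non-physician"; its only other level is the biostatistician. The Discussion gives the reason for the timing of the questionnaire: "to prevent performance bias, patients will complete the DASH questionnaire prior to visits with the physician".

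**The concern.** Constant-Murley, elbow motion and complications need a clinician. The pain VAS, the RGTQ and the BRT do not: each is the patient's own judgement, and one asks whether the patient would choose the same treatment again. If these are gathered by the treating side at the consultation, answers may be softened out of courtesy or coloured in recording, and this need not be equal in the two arms.

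Pain has a particular asymmetry. Under the criteria for early crossover, unacceptable pain is one route to surgery, and that route exists only in the non-surgical arm. The crossover windows (6–12 weeks in SHAFT-Y, 12–26 weeks in SHAFT-E) include scheduled visits at 6, 12 and 26 weeks. A pain rating given to the physician at such a visit has a different setting from one given by a patient who has already been operated on.

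At stake is the credibility of between-arm comparisons on these secondary outcomes. The primary outcome is not at stake.

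**Working it through.** No arithmetic beyond a count applies. The check sets the list of outcomes against the two collection routes and then against the stated scope of blinding.

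**Step 1: the patient-reported instruments.** From the section on secondary outcome measures: DASH, EQ-5D-5L, CA questions, pain VAS, RGTQ, BRT. That is 6.

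**Step 2: the route for each.**

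| Instrument | Named in the pre-visit package? | Left for the visit, literal reading | Left for the visit if CA means all anchor questions |
|---|---|---|---|
| DASH | yes | no | no |
| EQ-5D-5L | yes | no | no |
| CA questions | yes | no | no |
| Pain VAS | no | yes | yes |
| RGTQ | no | yes | no |
| BRT | no | yes | no |

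Literal reading: 6 − 3 = 3 instruments left to the physician. Loose reading: 6 − 5 = 1.

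**Step 3: which reading the text favours.** The umbrella term in the outcome list is anchor questions, with three named kinds beneath it. CA, RGTQ and BRT each have their own abbreviation, response format and question set, and the abbreviation list enters them separately, with CA as clinical anchors. The pre-visit sentence uses the narrow abbreviation CA and not the umbrella term. The literal reading is therefore the better one, but it is reached by elimination. The timeline figure, which might settle it, is not shown.

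**Step 4: is the person at the visit blinded?** The Blinding section covers the primary outcome and the biostatistician. Nothing describes keeping the visit physician unaware of allocation. The remark in the Discussion about blinding the physician follows from DASH being completed beforehand, so it concerns the DASH answers and not the treatment given. Several of the RGTQ name the operation or the non-surgical treatment in their wording.

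**Step 5: is the safeguard applied consistently?** The Discussion treats completion ahead of the physician contact as protection against bias. The CA items on current arm function and arm pain receive that protection. The RGTQ items on change in the same arm function and arm pain, read literally, do not. The document gives no reason for the difference.

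**The case against.** The strongest reply is that the article never says who collects the pain VAS, RGTQ or BRT. The phrase about additional measures has obvious referents that do need a clinician, and a condensed article may leave form-level detail to the full protocol. This stands in part. The list is an inference, and the RGTQ and BRT drop out if CA was shorthand. It does not rescue the pain VAS, which is outside the pre-visit list on either reading. The article also does more than stay silent: it fixes a two-route procedure and names what goes by the first route.

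A second reply is that similar content is already protected. The CA set, answered before the visit, includes a rating of upper-arm pain and a rating of the treatment result. This stands, and it lowers the stakes.

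A third is that patients are unblinded whatever the route, so moving the items removes only the added influence of the physician. This also stands.

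Some stronger readings are tempting, but the document does not support them:

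- A reader might infer that the physician interviews the patient aloud, with scar or brace in view. The text says only that the physician collects the measures at the consultation. Self-completion there is possible, and by Table 1 the brace would usually be off well before 52 weeks.
- A reader might see a contradiction with the assessor-blinded design. The Abstract and the Blinding section tie assessor blinding to the primary outcome, so the label in Trial design is merely too broad.
- A reader might suppose that the anchor questions will be used to interpret DASH change. The article does not say so; the DASH thresholds of 7 and 10 points are fixed in advance on other grounds.
- A reader might cite the earlier trial, described in the Background, that gave up randomisation because of physician preference. That concerned treatment allocation, not answers at follow-up.

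**Conclusion.** The point holds as an avoidable weakness in how some secondary outcomes are collected. It covers the pain VAS with confidence, and the RGTQ and BRT on the literal text: three of six patient-reported instruments, or one of six if CA was meant broadly. It rests on two inferences: that what is not named in the pre-visit package falls to the physician, and that a physician not described as blinded to allocation knows it.

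The size and direction of any bias cannot be derived. One could assume that 5–10% of patients in one arm move from no to yes on the BRT and conclude that the between-arm difference shifts by 5–10 percentage points, but that only restates the assumption. Nor does the point reach every visit for every item: the RGTQ and BRT look back on treatment and have little meaning at baseline.

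The primary DASH comparison is unaffected. The change is still worth making, because the protocol already accepts the principle and already has the means.

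**What to change.** Add the pain VAS, RGTQ and BRT to the email or mail package that already carries DASH, EQ-5D-5L and the CA questions, at the follow-up visits where each applies, with the same trial-worker completeness check before the consultation. State that the physician collects only what depends on an examiner or clinician: Constant-Murley, elbow range of motion and complications. If CA was meant to cover all anchor questions, say so in the same sentence; the pain VAS still has to be added.

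In Trial design, limit the assessor-blinded label to the primary outcome, in line with the Abstract and the Blinding section.

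The cost is a REDCap form change, a sentence or two of protocol text and a slightly longer questionnaire for the patient. No extra staff role is needed. If visits have already taken place under the present procedure, record the mode of collection for each visit so that the change can be examined.
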